### Safety

To investigate adverse effects, the participants will be asked at the end of each session whether they experienced effects such as “tingling”, “burning”, “headache”, “somnolence”, among others and subsequently asked the intensity of this sensation (1—none, 2—mild, 3—moderate, 4—strong) and whether this effect could be related to stimulation using a Likert scale ranging from 1 (unrelated) to 5 (strongly related). Although tDCS is considered a safe technique that has been applied to several neurological and psychiatric disorders for years (Nardone et al., 2015), if the patient exhibits any severe impairment or discomfort, treatment will be discontinued, and medical assistance and physical and psychological therapy will be provided to control potential problems and promote recovery.

### Participants

The evaluation and intervention procedures applied to the participants will be performed by trained professionals with experience in AD patient management. The team will consist of neuropsychologists, geriatricians, neurologists, occupational and speech therapists, biomedical and physiotherapists.

#### Inclusion Criteria

The participants will be included according to the following eligibility criteria: (a) being 50–90 years of age; (b) having a diagnosis of dementia [criteria of the Diagnostic and Statistical Manual of Mental Disorders—Fourth Edition (Text Revision, DSM-IV-TR; American Psychiatric Association, 2000)] and of probable AD according to the National Institute of Neurology and Communication Disorder and Stroke-The AD and Related Disorders Association Criteria (NINCDS-ADRDA; McKhann et al., 2011); (c) having a score = 1 in the Clinical Dementia Rating (CDR; Morris, 1993); (d) a score higher than 18 points in the Mini-Mental State Exam (MMSE; Folstein et al., 1975); (e) using acetylcholinesterase inhibitors (AChEI) and/or memantine for at least 3 months prior to screening; and (f) not having received regular cognitive intervention in the 3 months prior to the start of this clinical trial.

#### Exclusion Criteria

Participants (a) with unstable medical conditions, serious metabolic and/or cardiac diseases, alcoholism, focal neurological disorders (e.g., epilepsy, stroke, brain injury or tumor) and associated psychiatric disorders; or (b) using hypnotics and benzodiazepines up to 2 weeks before the start of the study; or (c) with any condition (e.g., *communication*, sensory or motor deficits) that could significantly interfere with the neuropsychological assessment or to receive a cognitive intervention protocol of the trial will be excluded from the study. In addition, participants with contraindications to fMRI scans such as claustrophobia, presence of electronic implants (transient or definitive pacemaker, cochlear implant), or the presence of intracranial aneurysm clips will also be excluded. Finally, exclusion criteria relating to contraindications of neurostimulation will be applied, following the safety guidelines: (a) using psychoactive drugs, as stated in the recommendations; (b) having implanted metallic or electronic devices; (c) having a cardiac pacemaker, seizures, acute eczema under the electrodes; and (d) the presence of tumors, epilepsy, or substance abuse (Nitsche et al., 2003; Brunoni et al., 2011).

#### Patient Recruitment

A sample of volunteer participants will be recruited from neurorehabilitation clinics, community programs dementia treatment centers and the Aging Neuropsychology Service (SENE) of the Federal University of Paraíba. The clinical trial will also be promoted in websites, newspapers and radio. Furthermore, healthcare professionals from the aforementioned sites will promote the study among patients with probable AD. After signing the informed consent form, the data of patients interested in participating in the clinical trial will be analyzed, and the patients will be contacted for inclusion in the study, according to the eligibility criteria.

### Intervention

#### tDCS

Anodal tDCS (2 mA, 30 min) will be applied three times a week for 2 months (24 sessions). The TCT-Research neurostimulator, developed by TransCranial Technologies (Hong Kong, China) will be used. The rubber electrodes are involved in saline-soaked sponges and fixed with a headband. We will use a specific electrode (4 × 4 cm) to avoid covering of adjacent areas by the tDCS electrode (current density = 0.13 mA/cm^2^). After the electrodes placement, the stimulation duration, current intensity and both ramp up/ramp down times will be programmed. To avoid that stimulation fail, the impedance levels will be checked (constant under 5 kΩ). Proper and reliable stimulation requires good contact under the electrode area to a consistently conductivity through the circuit. In the case of stimulation failures, the problem can be solved by reapplying a saline solution or conductive gel on the holding bags, or by parting the hair beneath electrodes, as reported in previous studies. To ensure that any discomfort occurs, the participants will be accompanied during all experiment procedures (DaSilva et al., 2011; Thair et al., 2017).

The active current will be applied to six cortical areas affected by AD. These sites are primary centers involved in the manifestation of clinical symptoms of the disease, including the left and right portions of the dorsolateral prefrontal cortex, related to short-term and long-term memory, judgment ability and executive functions; Broca’s area and Wernicke’s area, located in the temporal lobe, responsible for language; and the right and left somatosensory association cortex, in the parietal lobe, related to topographical and spatial orientation and praxis (Figure 1). The choice of these areas follows previously-tested neurostimulation protocols in patients with AD (Bentwitch et al., 2011; Rabey et al., 2013).

**Figure 1 F1:**
[figure not shown]
Montage of transcranial direct current stimulation (tDCS) sessions (Left Hemisphere). **(A)** F3—Dorsolateral prefrontal Cortex; **(B)** F5—Broca’s area; **(C)** CP5—Wernicke’s area; **(D)** P3—Somatosensory association cortex. Electrode position nomenclature of 10/20 System (Electroencephalography).

We will subdivide the neuromodulation protocol into A and B to stimulate the areas with the same number of sessions: (1) protocol A will involve stimulating Broca’s area (F5), Wernicke’s area (CP5), and the right dorsolateral prefrontal cortex (F4); and (2) protocol B will involve stimulating the left dorsolateral prefrontal cortex (F3) and the right and left portions of the parietal cortex (P4 and P5), according to the international 10–20 electrode nomenclature system. The protocols will be applied alternately; that is, protocol A will be applied in one session and protocol B in the next to stimulate the six cortical areas. The counterbalancing is justified to prevent higher current intensity applied to the patient’s scalp with the simultaneous stimulation of multiple areas, which could provoke painful stimuli and would not be in line with the technique guidelines (Furubayashi et al., 2008; Bikson et al., 2016).

The location of the protocol’s target regions to be applied on the day (either protocol A or B) will be performed before we begin the procedure. Thus, all regions are marked on the participant’s scalp in advance, avoiding delays during the treatment session. The instrument will cease after the first 10 min, and the electrodes will be positioned in the next region. As they are already marked, moving from one location to another will take less than 1 min (20–35 s estimate). Therefore, the treatment session will last at least 28 min, considering two brief stops for positioning the electrodes. We did not find evidence in the literature of interruptions of less than 1 min during electrode exchange or positioning, which could result in ablation or interference in the anode or current cathode effects.

Each aforementioned area will be stimulated for 10 min, totaling 30 min of treatment (three areas stimulated per session). The reference electrode 35 cm^2^ (5 × 7 cm) will be placed in the contralateral supraorbital area. The placebo stimulation protocol will be identical, although the device will cease to emit a current 30 s after starting the stimulation. Thus, the active current is simulated (slight tingling and itching sensation) for a short period, and the effects disappear shortly after the start of the stimulation (Nitsche et al., 2003; Gandiga et al., 2006).

An *fMRI* of all participants will be obtained before the experiment. The FSL software (FMRIB’s Software Library, University of Oxford, UK) will be used to transform coordinates for brain areas for each subject individually. The individual structural images will be initially converted into MNI coordinates (standard Montreal Neurological Institute) and then the MNI coordinates will be inversely transformed to the original imaging space. These values will be obtained by converting Talairach coordinates to the MNI space (Paus, 1996). These coordinates will be used to guide the frameless stereotaxy (Brainsight system, Rogue Research, Montreal, QC, Canada). The location of target regions will be performed by an experienced and trained professional. Procedures will be repeated at each treatment session for all participants involved.

#### Cognitive Intervention

The active protocol, involving 72 cognitive activities, was developed by neuropsychologists specialized in the non-pharmacological treatment of AD and will be applied by professionals trained in the management of this cognitive intervention program. This program is supported by similar studies of cognitive intervention in this population (Spector et al., 2001; Fernández-Calvo et al., 2010, 2015).

The cognitive activities with correspondence to the stimulated areas were developed using validated paradigms: (a) syntax and grammar tasks for Broca’s area and comprehension of lexical meaning and categorization for Wernicke’s area; (b) verbal and spatial working memory tasks for the dorsolateral prefrontal cortex; and (c) Spatial attention and perceptual–motor tasks (shapes and letters) for the somatosensory association cortex (e.g., Dobbs and Rule, 1989; Gabrieli et al., 1996; Buck et al., 1997; Thompson-Schill et al., 1997; Grossman and Rhee, 2001; Grossman et al., 2002; Love and Oster, 2002; Hao et al., 2005; Sparing et al., 2008; Bellgowan et al., 2009; Hamidi et al., 2009; Nyberg et al., 2009; Belleville et al., 2011; Hampstead et al., 2011). Most of these paradigms were applied in studies with AD patients or with neurostimulation techniques. Similar tasks based on the same paradigms were tested in studies that combined neuromodulation and cognitive intervention for people with AD (e.g., Bentwitch et al., 2011). However, some of these tasks have been adapted from the original paradigms to be used in pencil-and-paper activities. Some of the cognitive activities that will be used with the participants of the clinical trial are described below:

***Cognitive activities associated with Broca’s area***. This set of tasks tries to activate verbal language production through stimulating syntactic and grammatical language processing:-**Repeating words, pseudowords and phrases**. The participant should repeat the words (concrete nouns that vary in size and frequency), pseudowords and phrases created from the previous stimuli, which are presented orally.-**Naming**. The participant is instructed to retrieve the name of the displayed object. If the participant does not name it (e.g., bed), then both semantic (e.g., a piece of furniture) and phonological tips will be provided (e.g., begins with ca).-**Description-Narrative by confrontation**. This task consists of stimulating expressive conversation language based on visual stimuli. The participant will be shown a thematic slide about a situation and the situation should describe what they see, producing a story. It is about creating phrases and producing descriptive narratives and not simply naming objects in the image. For example, from the thematic sheet 1: “The city” can be elaborated into a story like the following: The girl went out to the street … She was going to buy … She arrived at the traffic light … She crossed the street without looking at the traffic lights … The driver … had to brake abruptly … The blind man was in the same …”***Cognitive activities associated with Wernicke’s area***. This type of activity focuses on triggering language comprehension using the lexical/semantic system:-**Sentence comprehension**. This task consists of silently reading incomplete sentences and the participant should write the word that completes the sentence (e.g., dogs have four‥.). If the participant does not give an answer, four words (e.g., fingers, legs, legs, eyes) are shown and the participant must select the one that best serves to complete the sentence. One variant of this task is understanding contextualized phrases, which consists of understanding phrases contextualized by images. The participant should read a sentence, analyze the images and mark the one that best represents the read sentence (e.g., the phrase “The driver drives the bus” appears next to four pictures, in which only one corresponds to the sentence read).-**Association of nouns and adjectives**. In this task, different nouns and adjectives are presented and the participant should join the most appropriate adjective for each word with the arrows (e.g., teeth, green, hair, fair, litigation, maturity, grassland, white, fruit, gray-haired).-**Grammatical class change**. This task consists of exchanging nouns for verbs and verbs for nouns. In changing the condition from noun to verb, participants are instructed to read the noun and retrieve the verb (e.g., Forgiveness = forgive). In the case of not issuing a response, a list of verbs will be shown in which the participants will retrieve the verb corresponding to the noun. In the condition of verb for noun, participants should read the verb and retrieve the corresponding noun (e.g., amar = lover).***Cognitive activities associated with left or right dorsolateral prefrontal cortex***. These activities are focused on promoting manipulation of verbal and spatial knowledge, associative processes and information selection:-**Object-location memory**. This task includes the coding and recognition stages of alternating stimuli or sites. In the coding and recognition phases, different sequences of six stimuli (shapes, colors, faces and letters) are presented. The stimulus memory task requires the subsequent recognition of target stimuli regardless of location, while the spatial task requires the coding and subsequent recognition of the location at which the stimuli were presented.-**Delayed match-to-sample tasks**. This type of activity requires visual pairing with the delayed model. The procedure consists of presenting a stimulus that the participant must remember (sample). Then, the stimulus is withdrawn and the participant must identify the stimulus that exactly corresponds to the sample (comparison stimulus) among a set of stimuli. The target and comparison stimuli can be simple (pictures of shapes, colors, letters, faces and objects) or complex (abstract). Thus, different variations of this task were created.-**Selection of semantic knowledge**. This task consists of classifying designs of common objects while taking into account different selection conditions such as a specific attribute of the object’s representation (large, small, light, heavy, artificial, natural, expensive, cheap) or according to the object’s name (spider, hammer). As an example of the first condition, a drawing of a car is presented together with the word car, whereas in the second condition the word spider is next to the drawing of a swan. In both activities, the participants should determine whether this classification is correct or not.-**Associative face memory**. This task requires encoding and recognizing associations between faces and names. In the first condition, subjects visualize paired faces with an unusual name. After the participant observes four pairs of faces with their names, one face and four name options are displayed.-**N-back task**. This task requires the participant to decide whether each heard or seen sequential stimulus matches what was heard or seen *n* items before. The stimuli can be letters, numbers, words (auditory condition) or photographs of objects (animals, fruits, tools, household utensils), and three conditions are used for each type of stimulus (*n* = 0, *n* = 1 and *n* = 2). For example, in condition *n* = 0, the participant must repeat the letter or (number) immediately after listening to it [C (“C”), F (“F”). T (“T”), S (“S”), B (“B”)]; in *n* = 1, the participant should say the letter they heard immediately before [C (“none”), F (“C”). T (“F”), S (“T”), B (“S”)]; and in *n* = 2, the participant has to say the letter they heard two times before [C (“nothing”), F (“nothing”), T (“C”), S (“F”), B (“S”)].-**Encoding and retrieving word meaning**. This task requires remembering words using a semantic coding strategy. The implemented stimuli are concrete (e.g., cat, notebook) and abstract nouns (e.g., beauty, fear) and the participant must judge whether each word refers to something abstract or concrete. Once the judgment of each word presented has been completed, the participant is asked to remember the most words they can.***Cognitive activities associated with somatosensory association cortex***. These exercises aim to stimulate cognitive components related to perception (e.g., recognition of simple and complex objects or spatial relationships between them), spatial attention (e.g., visual scanning and tracking), visual episodic memory (e.g., task retrieval), visual working memory (task recognition) and motor skills or spatial reasoning:-**Match-to-sample task**. This activity requires simultaneous visual matching capability. It consists of simultaneously displaying a simple or complex visual stimulus (sample) and four comparison stimuli. The participant should select the stimulus that exactly corresponds to the sample. The target and comparison stimuli can be simple (line drawings or pictures of shapes, letters, faces, or objects) or complex (abstract). Thus, different variations of this task were created.-**Visual search**. This type of activity requires the selection of relevant stimuli (target) and ignoring irrelevant (distracting) stimuli. The task requires the participant to detect the predefined target stimuli in a matrix in the midst of a series of distracting items. Different versions of this task were created using different types of stimuli (pictures and line drawings of shapes, letters, or objects). Two classes of stimuli are present in some situations in the matrix, requiring them to link characteristics to perform the activity. For example, the target is a vertical red bar and the distractors are vertical green bars and red horizontal bars.-**Overlapping figures**. This task requires identifying overlapping stimuli (shapes, letters and line drawings) with different levels of noise.-**Visual Tracking**. This task requires following a curved and irregular line with their eyes from one attached point to another attached point associated with numbers or letters. For example, the participant must choose a letter (or number) and follow the connecting line to its destination number (or letter) using only their eyes, without paying attention to the lines that they cross.

The 72 cognitive activities distributed by the stimulated areas each week were organized in a book, which includes the description (objective and procedure) and the material needed for each activity. All occupational therapists will be trained to apply each cognitive activity in the same way before beginning the clinical trial. Monitoring sessions will be held monthly to solve any problems in the intervention.

All activities will be applied simultaneously with neurostimulation, that is, the occupational therapist will perform activities involving operational memory while the operational memory area is stimulated with tDCS; cognitive intervention activities will focus on language when stimulating the language cortical area, and so on so that neurostimulation is related to the cognitive task tested. The 10-min time per region will also apply to the cognitive intervention protocol, since tasks will be scheduled to last up to this time. Thus, when the device ceases to emit the current, the cognitive task will not be “interrupted”, but rather finalized, because we expect to perform three different types of exercises over 30 min, each lasting 10 min. The pilot studies will allow us to calibrate a number of cognitive exercises necessary for each of these activities within each intervention session. Since the electrode change for a new region will be performed in less than 1 min, we think the interruption effect is minimal. Nevertheless, in order to minimize possible effects through the cognitive activity intervention, participants will be informed of the three groups of activities that will be performed at the beginning of each session, and the duration of each activity. However, even though the patient can perform them in a slower or faster time than this, we expect that this variation should be minimal because the total time is equivalent to the defined time in the protocol.

Regarding the placebo protocol of cognitive intervention, participants will watch short videos while receiving tDCS. The videos of the sham cognitive stimulation will also be chosen based on this time limit of 10 min. The researcher responsible for the cognitive intervention will stand next to the participant during the session and make comments unrelated to the treatment, including asking what the patient found from the video, whether it was pleasurable, and whether they are feeling comfortable.

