## Materials and Equipment

### Overview

NeuroAD is a factorial, placebo-controlled, double-blind and randomized clinical trial in which 100 patients at the mild stage of AD are randomly assigned to four groups: 1—active tDCS and active cognitive intervention; 2—sham tDCS and active cognitive intervention; 3—active tDCS and placebo cognitive intervention; and 4—sham tDCS and placebo cognitive intervention. All of the patients will be subjected to tDCS and cognitive intervention applied for 24 workdays. At the end of the trial, patients who received active tDCS and achieved clinical response will be invited to maintain tDCS bimonthly for 12 months, as part of a long-term study of tDCS for AD; those who did receive sham tDCS and did not respond will be offered 24 open-label daily sessions of tDCS (crossover study); finally, those who showed response with cognitive intervention (real or placebo) and sham tDCS will be referred to other neuropsychological centers specialized in treating dementias in our Institution.

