### Randomization and Blinding

The participants will be randomized into 1:1:1:1 blocks using the random number generator of an open-access randomization software program^1^. This sequence will be remotely performed by a blind researcher not involved in other research procedures. After the randomization process, a blinded staff member will perform patient allocation between the groups. Hidden allocation will be performed with closed, sealed and sequentially numbered envelopes. The participants will be identified by codes and will also be blinded; that is, they will ignore the arm of the study to which they will be allocated. The evaluation and treatment will be performed by independent researchers, who will identify the patients by their respective codes and will be blinded to the other research procedures. Data analysis will be performed by a professional not involved in any stage of patient recruitment, screening, assessment, or intervention. The effectiveness of the masking will be assessed after completing the treatment by interviewing the raters, who will be asked what type of treatment (active or placebo) they believe that the patient received. The relatives of participants will also be blinded and asked, at the end of the treatment, to which group they believe that the patient was allocated. The patients will also be asked questioned about which group they believe have been allocated. We decided to assess the effectiveness of the blinding by asking the relatives and/or caregivers of the patients because the patients have mild AD.

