#### Secondary Outcomes

##### The Neuropsychiatric Inventory Questionnaire (NPI-Q; Kaufer et al., 2000)

This instrument is completed by caregivers and provides information regarding 12 typical behavioral and psychological symptoms that may occur in patients with dementia. In this study, we used a severity rating (1 = mild, 2 = moderate, 3 = severe) for identified symptoms, deriving a severity score (range 0–36), with zero indicating no neuropsychiatric symptoms. The reliability and validity of this modified NPI score have previously been established.

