##### The Disability Assessment for Dementia (DAD; Gélinas et al., 1999)

This instrument is an informant-based scale composed of 17 items pertaining to basic ADLs (hygiene, dressing, continence and eating) and 23 items pertaining to instrumental ADLs (meal preparation, telephoning, going on an outing, finance and correspondence, medications and leisure and housework). Each item is evaluated for initiation, planning and effective execution. To avoid bias toward certain activities (e.g., meal preparation), nonapplicable questions are omitted from the final score, and the score is reported as a percentage. The maximum total score is 100, with lower Disability Assessment for Dementia (DAD) scores denoting greater impairment. Basic ADL and instrumental ADL subscores are included in the analysis, in addition to total DAD scores (Bahia et al., 2010).

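### The unqualified double-blind claim is not supported for the cognitive factor: exercises and videos are visibly different, and caregiver masking is asserted but not secured

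*Protocol article*

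**What the plan says.** The Overview describes the design without qualification: "NeuroAD is a factorial, placebo-controlled, double-blind and randomized clinical trial in which 100 patients at the mild stage of AD are randomly assigned". The four groups come from crossing active or sham tDCS with active or placebo cognitive intervention. The Abstract and the phase I description under Stepwise Procedures also use the double-blind label for the trial as a whole.

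Randomization and Blinding states: "The participants will be identified by codes and will also be blinded; that is, they will ignore the arm of the study". It adds: "The relatives of participants will also be blinded and asked, at the end of the treatment", for their view of the patient's group.

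The Cognitive Intervention section then sets out the two conditions. In the active condition a therapist leads three types of exercise of 10 minutes each during stimulation, and "participants will be informed of the three groups of activities that will be performed at the beginning of each session". In the placebo condition, "Regarding the placebo protocol of cognitive intervention, participants will watch short videos while receiving tDCS", while a researcher stays alongside and makes comments that have nothing to do with treatment.

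Of the secondary outcomes, the NPI-Q entry says "This instrument is completed by caregivers and provides information regarding 12 typical behavioral and psychological symptoms", and the DAD entry says "This instrument is an informant-based scale composed of 17 items" for basic activities, plus further items for instrumental ones. The Zarit interview measures the caregiver's own perceived burden. The CSDD is administered by a clinician from patient and caregiver information. Proposed Analysis applies the same strategy to all secondary outcomes as to ADAS-Cog.

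**The concern.** The label covers both randomised factors, but the described procedure can deliver masking for only one. tDCS has a true sham: the same montage, with the current stopped after 30 seconds. Nothing comparable exists for the cognitive factor, because doing naming, n-back or sentence-completion tasks cannot be mistaken for watching a video.

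What is at stake is the standing of any cognitive effect on behaviour, mood, function or caregiver burden. The Introduction's combination hypothesis names functional capacity and affective and behavioural change, and the scales for these draw on caregivers or other informants. If a caregiver learns which activity the patient did and forms an expectation from it, the reported difference mixes treatment with expectation. Under the present wording it would still be published as a double-blind, placebo-controlled result.

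**Working it through.** The document gives no figure for masking, so the check compares its statements and then traces which contrasts are exposed.

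**1. Who can be masked to the cognitive factor**

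| Person | What the article states | What the procedure allows |
|---|---|---|
| Person delivering sessions | Treatment and evaluation staff are independent; each is blinded to the other procedures | Must know: leads the exercises or sits beside the video |
| Patient | Blinded to arm | Sees the content at each of 24 sessions of about 30 min (24 × 0.5 h = 12 h); masking rests on not inferring which content is the placebo |
| Relative or caregiver | Blinded to arm | Not said to attend; no step described that keeps session content from them. Patients have mild AD (CDR 1, MMSE above 18) and may describe it |
| Outcome assessor | Treatment-blinded (Stepwise Procedures) | Can hold, provided that session content is not disclosed |

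**2. How many patients are concerned.** Randomization and Blinding says "The participants will be randomized into 1:1:1:1 blocks", and Sample Size gives 25 per group. Groups 1 and 2 receive active cognitive intervention and groups 3 and 4 the placebo, so the split is 25 + 25 = 50 against 25 + 25 = 50.

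**3. Which outcomes are exposed.** NPI-Q, DAD and Zarit rest on the caregiver or informant. CSDD is exposed only through its patient and caregiver input, since a treatment-blinded clinician rates it. BDNF is a serum assay. The rater's blinding for ADAS-Cog is not undermined, although a patient's expectation could still affect effort on the test.

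**4. Which contrasts are exposed.** Let b be an additive reporting bias that comes with the exercise condition. Groups 1 and 2 then carry b, and groups 3 and 4 carry 0.

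- Cognitive main effect: (b + b)/2 − (0 + 0)/2 = b
- Group 1 v group 3 (combination v tDCS alone): b − 0 = b
- Group 1 v group 2 (combination v cognitive alone): b − b = 0
- tDCS main effect: (b + 0)/2 − (b + 0)/2 = 0
- Interaction, (1 − 3) − (2 − 4): b − b = 0

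**5. Illustration of consequence, with b assumed.** For 50 v 50, no true effect, a two-sided 5% z test and b in SD units, the shift in the test statistic is b/√(2/50) = b/0.2. The false-positive rate is 1 − Φ(1.96 − b/0.2) + Φ(−1.96 − b/0.2).

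| Assumed b (SD) | False-positive rate |
|---|---|
| 0 | 5.0% |
| 0.1 | 7.9% |
| 0.2 | 17.0% |
| 0.3 | 32.3% |
| 0.5 | 70.5% |

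The document supplies no value for b, so this shows sensitivity only.

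**6. Whether the planned check would reveal the problem.** Raters are asked one active-or-placebo question. In group 2 (sham tDCS, active cognitive) and group 3 (active tDCS, placebo cognitive) either answer is partly right. Relatives and patients are asked about the group. Proposed Analysis compares correct with wrong responses by chi-square and does not separate the two factors.

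**The case against.** The strongest reply is that seeing the content of a session is not the same as knowing the allocation. The videos are built as an attention control: they fit the same 10-minute limit, stimulation or sham is given alongside, and a researcher is present and talks with the patient. Nothing says that patients or caregivers are told which activity is the placebo, or that caregivers attend. The sentence on announcing activities is written about the exercises, and whether the videos are introduced in the same way is not stated. Assessors are masked, evaluation and treatment staff are separate, and raters, relatives and patients are all asked to guess allocation.

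Much of this stands. A reader might infer that the caregiver-informed outcomes are simply open-label for the cognitive factor. The document does not support that: it asserts that relatives are blinded and describes no route by which they must learn the allocation. Nor does it support treating four of the five secondary outcomes as equally unmasked, since the CSDD is clinician-rated. It is also wrong to say that the whole combination question is affected, because group 1 v group 2 and the interaction are free of an additive bias.

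What the reply does not rescue is the label. The deliverer's masking is impossible, the patient's depends on not drawing an easy inference over 24 sessions, and the caregiver's is stated without support. The planned guess check earns credit, but as described it does not test each factor.

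**Conclusion.** The concern holds in a limited form. For the cognitive factor the trial is assessor-blinded. Masking of the deliverer is impossible, masking of patients is not credible, and masking of caregivers is at risk. The exposed results are the cognitive main effect (50 v 50) and group 1 v group 3 (25 v 25) on NPI-Q, DAD and Zarit, and on CSDD in part. The tDCS factor, BDNF, rater blinding of ADAS-Cog and group 1 v group 2 are not undermined.

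The size of the bias cannot be derived from the document, and the false-positive rates above hold only for the assumed values of b. That group 1 v group 2 and the interaction escape rests on the bias being additive, that is, the same whether the tDCS is active or sham. The point deserves correction because it changes what the trial may claim; it does not invalidate the primary outcome.

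**What to change.** - In the Abstract, Overview, Randomization and Blinding, and the phase I description under Stepwise Procedures, describe the trial as double-blind for tDCS and assessor-blinded for the cognitive factor.
- In Randomization and Blinding and in Proposed Analysis, have raters, relatives and patients guess tDCS allocation and cognitive allocation as two separate questions, and analyse each.
- Before each assessment, instruct patients and caregivers not to tell raters what was done in sessions.
- Report effects of the cognitive factor on NPI-Q, DAD, Zarit and CSDD as not securely masked, and rest claims of cognitive efficacy on the blinded-rater ADAS-Cog.

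The cost is wording, one extra question per respondent and a short instruction at assessments. Randomisation, sample size and the primary analysis stay as they are. The real price is a weaker claim for the cognitive factor on the caregiver-informed outcomes.
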